# Intermittent Theta Burst Stimulation Combined with Cognitive Training in Mild Cognitive Impairment: Protocol for an 18-Week Randomised, Double-Blind, Sham-Controlled Feasibility Pilot Study (The iCog.X Boost Trial)

**DOI:** 10.3390/mps9050130

**Published:** 2026-09-01

**Keywords:** cognitive training, mild cognitive impairment (MCI), transcranial magnetic stimulation (TMS), randomised controlled trial (RCT), dementia prevention

## Abstract

**Introduction:** Mild cognitive impairment (MCI) is a transitional stage between normal ageing and dementia, affecting ~35% of adults aged 70+ and carrying a 15–18% annual risk of progression. Cognitive training (CT) shows promise but outcomes are variable and transfer to daily function is unclear; intermittent theta burst stimulation (iTBS) may enhance prefrontal neuroplasticity. Few studies have evaluated whether combining CT and iTBS in MCI is practical, acceptable, and safe. **Methods:** This 18-week, randomised, double-blind, sham-controlled feasibility pilot trial will recruit 44 individuals with MCI, randomised 1:1 to CT + active iTBS or CT + sham iTBS. Participants complete 14 CT sessions over 10 weeks; accelerated iTBS is delivered in five sessions per day over five consecutive days at 75% resting motor threshold to the left DLPFC using neuronavigation, with reversed-coil sham. Primary outcomes are feasibility, acceptability, adherence, and safety; secondary (exploratory) outcomes are cognitive, functional, and psychological; tertiary (mechanistic) outcomes are EEG- and TMS-derived neurophysiological measures. The trial is not powered for efficacy: feasibility and neurophysiological outcomes will be analysed descriptively, while secondary outcomes will be analysed using linear mixed-effects models. **Ethics and dissemination:** Ethical approval has been granted by the Western Sydney University HREC (H16500); written informed consent will be obtained before enrolment. **Trial registration number:** ACTRN12625000952448.

## 1. Strengths and Limitations of This Study

This feasibility trial evaluates the combined delivery of intermittent theta burst stimulation and cognitive training in individuals with mild cognitive impairment.The primary focus on feasibility, acceptability, adherence, and safety outcomes directly addresses the gap in the evidence base prior to undertaking a definitive efficacy trial.Neurophysiological outcomes using EEG and TMS provide exploratory mechanistic data to inform the design of a future fully powered trial.The mixed delivery format, including home-based cognitive training, enhances accessibility and real-world feasibility for older adults.As a feasibility pilot, this study is not powered to detect treatment efficacy; cognitive and neurophysiological findings are hypothesis-generating only and should be interpreted with caution.

## 2. Introduction

Mild cognitive impairment (MCI), formally known as Mild Neurocognitive Disorder according to DSM-5-TR criteria [1], is characterised by a measurable decline in cognitive abilities, particularly in memory and executive functions, without significantly impacting daily functioning. MCI affects around 35% of adults over 70 [2], and carries a 15–18% annual risk of progression to dementia, which increases longitudinally [3]. MCI thus represents a critical window for intervention, with the potential to delay or prevent further deterioration and preserve independence.

Current pharmacological treatments, such as cholinesterase inhibitors and memantine, have demonstrated limited efficacy and are not approved for MCI due to modest benefit and side effects [4]. Anti-amyloid agents like aducanumab and lecanemab have shown minimal clinical efficacy and are restricted to amyloid-positive individuals [5]. These drugs carry risks including cerebral oedema and haemorrhage [6]. Non-pharmacological strategies therefore remain the primary mode of intervention.

Non-pharmacological approaches targeting modifiable risk factors such as lifestyle and cognition have received increasing attention [7], though cognitive benefits of interventions such as physical activity remain inconsistent [8]. Consequently, more targeted approaches that directly enhance cognition and support daily functioning are needed.

Cognitive training (CT) has emerged as a prominent intervention for MCI. CT involves structured tasks aimed at improving specific cognitive domains through repeated practice [9]. Strategy-based CT focuses on compensatory techniques such as visual imagery to support daily functioning [10], while computerised CT delivers adaptive exercises targeting memory, attention, and processing speed [11,12]. Combining both forms may offer complementary benefits in instrumental activities of daily living (iADLs) by addressing compensatory and restorative mechanisms in an engaging and more personalised approach [13].

While numerous studies show that CT can improve cognitive performance in memory, attention, and executive function [14], outcomes remain variable. Neuroimaging has demonstrated increased activation in frontoparietal regions and enhanced neural connectivity post-training, supporting underlying neuroplastic changes [15]. However, CT adherence can be challenging in MCI due to task repetition and fatigue [16], and the transfer of gains to real-world functional improvements remains inconsistent [17]. This highlights the need to optimise CT to better translate cognitive gains into daily life benefits.

Neuromodulatory techniques such as repetitive transcranial magnetic stimulation (rTMS) may enhance CT by priming cortical regions associated with cognitive control [18]. rTMS is a non-invasive brain stimulation that modulates cortical excitability by delivering electromagnetic pulses to the brain [19]. When applied to the dorsolateral prefrontal cortex (DLPFC), high-frequency rTMS can facilitate long-term potentiation-like effects and strengthen cognitive functions such as working memory [20]. Despite these benefits, standard rTMS protocols are time-consuming (up to 60 min per session for several weeks), which can limit feasibility and increase dropout, especially in older adults. Studies have highlighted that reducing session time may improve adherence and clinical outcomes [21].

Intermittent theta burst stimulation (iTBS) offers a more feasible alternative. iTBS mimics the brain’s natural theta rhythms (5 Hz) associated with memory and learning by delivering brief, high-frequency bursts in under 3 min [22]. This protocol enhances synaptic plasticity and cortical excitability [23], and when applied to the left DLPFC, has been shown to produce preliminary signals of cognitive benefit in individuals with AD and MCI [24]. Additionally, iTBS is safe and well-tolerated [25], making it a potentially feasible therapeutic strategy for people with MCI.

Neurophysiological measures provide complementary indices of the neural changes that may accompany combined iTBS and CT. iTBS applied to the left DLPFC is hypothesised to induce long-term potentiation-like plasticity that increases cortical excitability and modulates intracortical inhibition. TMS paired-pulse paradigms (short- and long-interval intracortical inhibition, SICI and LICI) provide measures of these intracortical inhibitory processes. EEG provides complementary markers of network function during rest and cognitive processing, including event-related potential components (e.g., N2 and P3) that are commonly associated with inhibitory control and attentional allocation during the Go/NoGo task, as well as aperiodic (1/*f*) activity derived from resting EEG, as a proposed marker of cortical excitation/inhibition balance. Examining these measures alongside cognitive outcomes may provide preliminary insight into whether intervention-related cognitive change is accompanied by changes in cortical excitability, inhibition, and neurocognitive processing. Given the feasibility design, these neurophysiological analyses are exploratory and hypothesis-generating rather than definitive tests of mechanism.

Preliminary studies combining CT with rTMS have reported cognitive benefits compared with CT alone [26,27]. However, most trials used lengthy, standard rTMS protocols rather than accelerated iTBS protocols. Few have specifically explored iTBS paired with CT in MCI populations. Existing studies are limited by small sample sizes, unstructured training protocols, no formal assessment of feasibility, acceptability, and safety, and the absence of neurophysiological outcome measures [28]. This feasibility pilot therefore aims to determine whether a combined CT+iTBS intervention can be delivered as planned in an MCI population and whether predefined progression criteria are met, while generating preliminary estimates of cognitive and neurophysiological outcomes to inform a future definitive trial.

## 3. Aims and Hypotheses

The primary aim is to evaluate the feasibility, acceptability, adherence, and safety of combining CT with iTBS in people with MCI. Secondary (exploratory) aims are to examine signals of change in cognition, functional capacity, psychological wellbeing, and health-related quality of life. Tertiary (mechanistic) aims are to explore neurophysiological changes associated with active versus sham iTBS using EEG and TMS, including measures of cortical excitability, inhibition, and cognitive processing. As an exploratory feasibility pilot, the trial is not powered to test efficacy. Secondary and tertiary outcomes are hypothesis-generating and will inform outcome selection and sample-size estimation for a future definitive trial. We hypothesise that the trial will meet the predefined progression criteria in Table 1 (recruitment, eligibility, adherence, tolerability, acceptability, and retention) and that the intervention will be delivered safely.

## 4. Methods

### 4.1. Study Design and Setting

This is an 18-week, randomised, double-blind, sham-controlled, parallel-group feasibility pilot trial conducted across two Western Sydney University research sites: NICM Health Research Institute and the School of Health Sciences. The trial comprises two arms: CT + active iTBS and CT + sham iTBS with 1:1 randomisation. Participants will undergo in-person assessments and stimulation sessions during the initial intervention phase, followed by a home-based cognitive training program using a secure, university-hosted online platform developed using the Flask web framework (Python 3.11). Data will be stored securely via REDCap (Vanderbilt University, Nashville, TN, USA), with remote coaching delivered through Zoom Video Communications, Inc. (San Jose, CA, USA) to support adherence. This protocol was developed in accordance with the SPIRIT guidelines and adheres to the CONSORT extension for randomised pilot and feasibility trials, as well as the principles of ICH E6 Good Clinical Practice.

### 4.2. Participants

Adults aged 55 to 85 years meeting the study criteria for MCI will be recruited. Eligibility criteria were developed in accordance with international TMS safety guidelines in research settings [29] and are summarised in Table 2.

### 4.3. Interventions

#### 4.3.1. iTBS Stimulation Protocol

Participants allocated to the active stimulation group will receive iTBS over the left DLPFC across 5 consecutive weekdays. Each day comprises 5 iTBS sessions, spaced 10 min apart, totalling 25 sessions and 3000 pulses/day. Stimulation will be delivered using a MagPro x100 (MagVenture A/S, Farum, Denmark) at NICM Health Research Institute, or a MagStim Super Rapid2 Plus1 (MagStim Co Ltd., Whitland, UK) at the School of Health Sciences, each with a 70 mm figure-of-eight coil. Coil placement is guided by the Brainsight Neuronavigation System (Rogue Research Inc., Montreal, QC, Canada), using the BeamF3 algorithm to localise F3 coordinates according to the international 10–20 EEG system. The coil is held tangentially at 45° to induce a posterior–anterior current.

Resting motor threshold (RMT) will be determined using single-pulse TMS over the primary motor cortex. Surface EMG will be recorded from the right first dorsal interosseous (FDI) muscle using Ag/AgCl electrodes (active electrode on the muscle belly, reference electrode on the right olecranon), amplified ×32,000, bandpass-filtered (20–1000 Hz), and digitised at 2000 Hz via a Micro1401 Data Acquisition System and Signal software (Cambridge Electronic Design, Cambridge, UK). The motor hotspot will be defined as the scalp site where at least 5 out of 10 pulses elicit a motor-evoked potential (MEP) ≥ 50 µV in the relaxed FDI [31]. RMT will be reassessed daily, with stimulation intensity set at 75% of RMT.

Each iTBS session follows the standard protocol: bursts of 3 pulses at 50 Hz repeated at 5 Hz (every 200 ms), delivered in 2 s trains with 8 s inter-train intervals, for a total of 600 pulses per session lasting approximately 3 min. This protocol adheres to international safety and reporting guidelines for TMS [29] and the TMS Methodological Checklist by Chipchase et al. [32]. Participants may continue stable medications that do not affect cortical excitability, but substances known to lower seizure threshold (antipsychotics and recreational drugs) will be prohibited during the trial.

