TMS assessments will include the determination of RMT. SICI and LICI will be assessed using standardised paired-pulse paradigms to probe intracortical inhibitory processes. The test stimulus will be calibrated to elicit an MEP of approximately 1 mV in amplitude in the FDI muscle of the right hand. For SICI, a 90% RMT conditioning stimulus will precede the test stimulus at ISIs of 2, 3, and 5 ms. For LICI, two suprathreshold pulses at 120% RMT will be delivered at ISIs of 50, 100, and 150 ms [46,47].

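### The only EMG gain stated (×32,000) does not fit the planned test MEP of about 1 mV unless the converter accepts about ±16 V or the paired-pulse recordings use another gain

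*Protocol article*

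**What the plan says.** Section 4.3.1 introduces the EMG set-up in its paragraph on motor threshold: "Resting motor threshold (RMT) will be determined using single-pulse TMS over the primary motor cortex". The signal from the right FDI is "amplified ×32,000, bandpass-filtered (20–1000 Hz), and digitised at 2000 Hz via a Micro1401 Data Acquisition System". The response criterion in that paragraph is "motor-evoked potential (MEP) ≥ 50 µV in the relaxed FDI".

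Section 4.5 covers the mechanistic TMS outcomes: "SICI and LICI will be assessed using standardised paired-pulse paradigms to probe intracortical inhibitory processes". It then fixes the size of the test response: "The test stimulus will be calibrated to elicit an MEP of approximately 1 mV in amplitude in the FDI muscle of the right hand". For LICI it gives the pulse intensity as 120% of RMT, but no response size.

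Section 4.5 states no EMG gain, filter or sampling rate, so the chain in 4.3.1 is the only one in the article. Neither section gives the converter's input range, says whether ×32,000 is an analogue gain, or says whether 1 mV is a peak or a peak-to-peak value.

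**The concern.** The gain suits a threshold response of 50 µV. The test response in 4.5 is twenty times larger (1,000 / 50 = 20) and comes from the same muscle. Multiplied by the only stated gain, it gives a voltage that a converter would have to be unusually wide to accept.

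SICI and LICI compare the size of a conditioned response with that of an unconditioned one. If the signal saturates, the larger, unconditioned response loses most, and the ratio moves toward 1, which reads as no inhibition. Section 4.4 intends these measures to show which neurophysiological markers are practicable and merit a place in the definitive trial, so a recording artefact could distort that choice. Table 4 schedules TMS at five timepoints, which is up to 44 × 5 = 220 sessions. Section 8 says recruitment is under way, and the true size of a clipped response cannot be recovered later.

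**Working it through.** The article states no output voltage, so there is no figure of its own to reproduce.

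**Inputs from the article**
- Gain G = 32,000 (4.3.1)
- Threshold criterion 50 µV (4.3.1)
- Test response about 1 mV (4.5)
- Filter 20–1000 Hz and sampling at 2000 Hz (4.3.1)

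**Assumptions**
- The chain in 4.3.1 also serves the recordings in 4.5.
- ×32,000 is the analogue gain ahead of the converter.
- The response is symmetric about zero and 1 mV is peak-to-peak.
- The converter range ±R is unknown and is taken as 2.5, 5, 10 and 16 V in turn.

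**Step 1. Output voltage = G × input.**
- Threshold response: 32,000 × 50 µV = 1.6 V peak-to-peak (±0.8 V). This fits every range tried.
- Test response: 32,000 × 1 mV = 32 V peak-to-peak (±16 V).

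**Step 2. Largest unclipped peak-to-peak response = 2R / G.**

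| Assumed range | Largest response at ×32,000 | Largest gain that holds 1 mV (2R / 1 mV) |
|---|---|---|
| ±2.5 V | 5 / 32,000 = 156 µV | 5,000 |
| ±5 V | 10 / 32,000 = 313 µV | 10,000 |
| ±10 V | 20 / 32,000 = 625 µV | 20,000 |
| ±16 V | 32 / 32,000 = 1,000 µV | 32,000 |

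A 1 mV response therefore clips at any range below ±16 V, and at ±16 V nothing is left for trial-to-trial variation. If 1 mV means a single peak, the range would have to reach ±32 V.

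**Step 3. Direction of the bias.** Let t be the true unconditioned size, c the conditioned size (c < t under inhibition) and L the ceiling from step 2, with t > L.
- If c ≥ L, both read L and the ratio is 1.
- If c < L, the ratio is c / L, which exceeds c / t.

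Either way the observed ratio is too close to 1.

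For illustration, take t = 1.0 mV and c = 0.5 mV. The value of c is assumed and is not in the article. The true ratio is 0.50.
- At ±5 V: 0.3125 / 0.3125 = 1.00.
- At ±10 V: 0.5 / 0.625 = 0.80.

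**Step 4. Sampling.** Half the sampling rate is 2000 / 2 = 1000 Hz, which equals the upper filter edge. There is no margin for the filter's roll-off.

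**The case against.** The strongest reply is that the gain is stated for a different measurement. It stands in the motor threshold paragraph, where it works, and 4.5 does not say that the paired-pulse recordings use it. An article condenses a fuller protocol, so a separate paired-pulse gain could exist there. The converter range is not given either, so clipping is an inference and not something the article states. All of this stands, and it makes the conclusion conditional. It does not remove the point: the article prints one specific gain for this muscle and a target response that this gain does not suit at any assumed range up to ±10 V.

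A second reply is that the fault would show itself. An operator calibrating to 1 mV on a system that saturates at 313 or 625 µV could not reach the target, so silent bias throughout the trial is unlikely. That is fair. It also suggests that the working gain may differ from the printed one, in which case the text needs correcting.

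A reader might go further and infer that MEPs in general clip, that SICI and LICI cannot be derived, or that most responses to the 120% RMT pulses are truncated. The article does not support these readings. Threshold responses fit easily, the gain used for SICI and LICI is not stated, and no response size at 120% RMT is given.

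**Conclusion.** The point holds conditionally. If ×32,000 is the analogue gain for the paired-pulse recordings, a 1 mV peak-to-peak test response needs about ±16 V, and at ±2.5 to ±10 V only responses up to about 156 to 625 µV are recorded intact. The target could then not be recorded, and SICI and LICI ratios would be biased toward no inhibition to the extent that responses exceed the ceiling. If another gain is used, or ×32,000 is a misprint or not an analogue gain, the article describes its recording chain wrongly or incompletely. In both cases the two sections must be reconciled.

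It would be wrong to infer that stimulation intensity is compromised: RMT, from which intensity is set, rests on a 50 µV criterion that gives 1.6 V. EEG, the secondary outcomes, the primary outcomes and the stop/go criteria in Table 1 are also untouched. SICI and LICI are tertiary, exploratory and descriptive, so the severity is minor to moderate.

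The sampling point is secondary. The filter edge sits at half the sampling rate and not above it, and the effect on MEP amplitude is probably small.

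**What to change.** 1. Confirm the gain, the converter's input range and the amplitude definition actually used for the paired-pulse recordings. Then either correct the gain in 4.3.1 or state a separate chain in 4.5, and say whether 1 mV is peak-to-peak.
2. Choose a gain and range that hold responses of several mV. As an example, at ×1000 a 1 mV response becomes 1 V, and an assumed ±5 V range spans 10 V / 1000 = 10 mV. With an assumed 16-bit converter, one step is 10 V / 65,536 / 1000 ≈ 0.15 µV, so a 50 µV response is still well resolved.
3. Inspect traces already recorded for saturation. Report how many SICI and LICI values are affected, by timepoint, and flag them as unreliable. Dropping only the clipped responses without saying so would remove the largest ones selectively and bias the remainder.
4. Optionally, sample well above twice the filter edge, for example at 5000 Hz, to gain anti-aliasing margin.

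The cost is a settings check, a short text correction and a review of existing traces. No visits are added, and files grow somewhat if the sampling rate rises. Whether any hardware change is needed cannot be judged from the article, which does not name the amplifier.

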#### 4.3.2. Sham iTBS Intervention

Sham stimulation will use the same figure-of-eight coil as the active condition, rotated 180° so only the edge contacts the scalp, limiting magnetic field penetration while preserving some auditory and somatosensory sensations. This method has been validated as a sham condition in prior research [33]. Setup will be performed by the unblinded laboratory technician.

#### 4.3.3. Cognitive Training Intervention

The iCog.X Boost Program is a 10-week, structured CT intervention for individuals with MCI. It includes 14 training sessions, delivered across two phases: 5 in-person sessions followed by 9 online sessions delivered via a secure online platform. Participants also attend 2 small-group psychoeducation sessions via Zoom Video Communications, Inc. (San Jose, CA, USA), covering cognitive ageing, strategy use, and real-world cognitive management.

The program targets memory, attention, reasoning, and problem-solving, commonly affected in MCI [34]. It combines explicit strategies, progressive task difficulty, and real-life applications. Sessions include guided exercises, and real-world generalisation tasks to support daily implementation.

The in-person phase introduces core strategies before participants transition to the independent online phase, where sessions reinforce and consolidate these strategies through repeated practice. Task difficulty is dynamically adjusted based on accuracy, speed, and adherence to maintain optimal engagement without cognitive overload. Real-time coaching is provided.

To facilitate adherence, participants receive weekly email reminders and follow-up calls. After 2 consecutive missed sessions, additional contact attempts will be made via 2 calls and 1 email. Participants missing 3 consecutive sessions without responses are withdrawn. A 2-week grace period will be provided to allow catch-up.

The intervention follows a scaffolded approach, gradually transitioning from foundational cognitive skills to higher-order executive functions. Following each session, participants complete home exercises to integrate strategies into daily life (e.g., writing and recalling a grocery list). The CT structure is illustrated in Figure 1 and a session-by-session breakdown is provided in Table 3.

Psychoeducation sessions cover cognitive changes in ageing, everyday challenges, and strategy application. Group delivery encourages experience sharing and social support, which may improve adherence, real-life transfer, and reduce isolation linked to cognitive decline in MCI [35].

